## Abstract

**Background:**

Traumatic brain injury (TBI) disrupts normal brain tissue and functions, leading to high mortality and disability. Severe TBI (sTBI) causes prolonged cognitive, functional, and multi-organ dysfunction. Dysfunction of the autonomic nervous system (ANS) after sTBI can induce abnormalities in multiple organ systems, contributing to cardiovascular dysregulation and increased mortality. Currently, detailed characterization of early autonomic dysfunction in the acute phase after sTBI is lacking. This study aims to use physiological waveform data collected from patients with sTBI to characterize early autonomic dysfunction and its association with clinical outcomes to prevent multi-organ dysfunction and improving patient outcomes.

**Objective:**

This data analysis protocol describes our pre-planned protocol using cardiac waveforms to evaluate early autonomic dysfunction and to inform multi-dimensional characterization of the autonomic nervous system (ANS) after sTBI.

**Methods:**

We will collect continuous cardiac waveform data from patients managed in an intensive care unit within a clinical trial. We will first assess the signal quality of the electrocardiogram (ECG) using a combination of the structural image similarity metric and signal quality index. Then, we will detect premature ventricular contractions (PVC) on good-quality ECG beats using a deep-learning model. For arterial blood pressure (ABP) data, we will employ a singular value decomposition (SVD)-based approach to assess the signal quality. Finally, we will compute multiple indices of ANS functions through heart rate turbulence (HRT) analysis, time/frequency-domain analysis of heart rate variability (HRV) and pulse rate variability, and quantification of baroreflex sensitivity (BRS) from high-quality continuous ECG and ABP signals. The early autonomic dysfunction will be characterized by comparing the values of calculated indices with their normal ranges.

**Conclusion:**

This study will provide a detailed characterization of acute changes in ANS function after sTBI through quantified indices from cardiac waveform data, thereby enhancing our understanding of the development and course of eAD post-sTBI.

## Introduction

1

Traumatic brain injury (TBI) is a heterogeneous condition that leads to significant injury-related disability and mortality (1). TBI not only impacts the brain but also results in extracranial multi-organ dysfunction, leading to secondary brain injuries and poor clinical outcomes (2). In 2014, TBI accounted for 2.8 million Emergency Department visits, 288,000 hospitalizations, and 56,800 deaths (3). One-third of survivors of hospitalization suffer long-term disability (3). The severity of TBI falls into three severity classifications based on the Glasgow Coma Scale (GCS) score following resuscitation: mild (GCS 13–15), moderate (GCS 9–12), and severe (GCS < 9), contingent upon criteria such as the duration of loss of consciousness, post-traumatic amnesia (4). However, variation in presentation, hospital course, and outcomes within each severity category is significant. Individuals initially diagnosed with mild or moderate TBI upon hospital admission may deteriorate, necessitating escalation in TBI management (5–7).

### Extracranial organ dysfunction and sympathetic activation following TBI

1.1

The pathophysiology of extracranial organ dysfunction following TBI is characterized by complex neuroendocrine and inflammatory cascades. The initial brain injury triggers an intense sympathetic activation, leading to a massive release of catecholamines and inflammatory mediators (8). This autonomic response creates a paradoxical situation: while the acute elevation in sympathetic tone may initially serve as a protective mechanism to maintain cerebral perfusion despite increased intracranial pressure, its persistence can lead to detrimental systemic effects (9).

The sustained sympathetic hyperactivity, which can persist for up to 10 days post-injury, results in circulating catecholamine levels that may be up to 10-fold higher than normal (8). This catecholamine surge serves to maintain cerebral perfusion pressure in the face of rising intracranial pressure, but simultaneously can induce direct cardiac injury through catecholamine-mediated myocardial damage, systemic inflammatory responses, immune system dysfunction and metabolic derangements. These mechanisms help explain why 22.3% of patients with isolated moderate-to-severe TBI demonstrate left ventricular dysfunction as early as 24 h after injury (10). When this cardiac dysfunction occurs in the context of impaired cerebral autoregulation (present in 40% of moderate-to-severe TBI cases), it can create a vicious cycle: decreased cardiac output leads to systemic hypotension, which further compromises cerebral blood flow and brain perfusion.

Recent research using clinical scoring systems, particularly the Sequential Organ Failure Assessment (SOFA), has quantified the burden of multi-organ dysfunction following TBI. Studies have shown that nearly 40% of patients with moderate to severe TBI develop multi-organ dysfunction syndrome (MODS) within the first 10 days of hospitalization, with predominant involvement of the cardiopulmonary systems (11). Furthermore, examination of SOFA scores within the initial 72 h post-admission revealed that 252 patients (68%) with moderate to severe TBI developed early MODS (12). Understanding these pathophysiological mechanisms and their temporal evolution is crucial for predicting MODS risk, providing early warning of clinical deterioration, and guiding therapeutic interventions.

The relationship between intracranial pressure (ICP), autonomic function, and hemodynamics in TBI follows distinct temporal patterns. In the acute phase, elevated ICP triggers an intense sympathetic response with increased catecholamine release, leading to systemic vasoconstriction and hypertension (13). This response can become particularly problematic in cases of refractory intracranial hypertension. As demonstrated in (14), refractory ICP elevations are associated with a marked dysregulation of autonomic function, characterized by persistent sympathetic hyperactivation, reduced heart rate variability, impaired baroreflex sensitivity and development of refractory arterial hypertension. These autonomic alterations can persist even after ICP normalization, suggesting a more complex pathophysiology than previously recognized. In the subacute phase, this initial sympathetic surge may be followed by autonomic exhaustion, leading to vasodilation and hypotension. Understanding these temporal patterns and their relationship to autonomic dysfunction is crucial for appropriate hemodynamic management in TBI patients.

### Heart rate variation with autonomic dysfunction

1.2

ANS critically regulates heart and vascular system functions by utilizing sympathetic and parasympathetic fibers directed toward the heart, alongside sympathetic fibers targeting the vessels (15). One hand, the release of norepinephrine from autonomic sympathetic fibers in heart induces positive inotropic and chronotropic effects through the activation of *β*-adrenoceptors. The other hand, acetylcholine released by parasympathetic fibers leads to negative inotropic and chronotropic effects by stimulating muscarinic receptors (16). In addition, the autonomic nervous system influences arterial blood pressure (ABP) and heart rate by producing oscillations in these cardiovascular parameters that occur at specific frequencies (16). In frequency domain analysis, the high frequency (HF, 0.15–0.4 Hz) component primarily reflects respiratory sinus arrhythmia (RSA) and is predominantly influenced by parasympathetic modulation, though respiratory parameters such as rate and tidal volume can significantly affect its interpretation. The low frequency (LF, 0.04–0.15 Hz) component and LF/HF ratio, previously considered markers of sympathetic activity or sympathovagal balance, actually represent an intricate interplay of both sympathetic and parasympathetic influences on cardiac autonomic control. Several factors contribute to LF power, including baroreflex-mediated autonomic fluctuations, central oscillations in sympathetic nerve activity, and mechanical effects of breathing at lower frequencies.

However, in the severe traumatic brain injury (sTBI) population, the interpretation of frequency-domain HRV metrics is complicated by several factors. Mechanical ventilation, often required for sTBI patients, can artificially alter respiratory patterns, impacting HF power and respiratory-related heart rate modulation. Additionally, the use of sedation and analgesic medications, common in sTBI management, can directly affect autonomic regulation and HRV patterns. Intracranial pressure fluctuations, characteristic of sTBI, can independently influence autonomic regulation and cardiovascular variability. Furthermore, hemodynamic management strategies involving vasopressors and fluid management can affect blood pressure variability and consequent autonomic responses. Baguley et al. investigated dysautonomia following sTBI based on the HRV analysis, finding significant differences in HRV among TBI patients, controls, and between dysautonomia and non-dysautonomia subjects (17). Froese et al. assessed the physiological relationship between pressure reactivity index (PRx) and HRV, BP, and baroreflex sensitivity (BRS) using time-series statistical methodologies in sTBI patients. They demonstrated a stronger connection between BRS, HRV, and PRx, indicating sympathetic autonomic response related to cerebrovascular reactivity derangements (18). Therefore, while these frequency-domain metrics provide valuable insights into autonomic regulation, their interpretation in sTBI patients should account for these confounding factors and be integrated with other autonomic assessment measures for a more comprehensive evaluation of autonomic dysfunction.

### Need for clinical tools to assess autonomic dysfunction in clinical care

1.3

Despite the high burden of extracranial clinical deterioration, multi-organ dysfunction, and early autonomic dysfunction following sTBI, there are no real-time clinical decision support (CDS) tools, early warning scores, guidelines, or studies to help clinicians predict which patients will develop MODS. The sTBI-related literature lacks robust and well-powered analysis of autonomic function using cardiac and ABP waveform data, often including only exploratory datasets. sTBI is associated with eAD, yet characterization of eAD and its impact on clinical outcomes, in large sTBI populations is lacking. To bridge this gap, this protocol outlines the waveform data analysis for eAD characterization post-sTBI using a large prospective cohort (collected within the confines of a multicenter randomized controlled trial). We propose examining granular cardiac waveform data to identify subtle changes in the ANS in patients following sTBI that precede visible clinical symptoms of MODS. These changes can serve as early indicators of autonomic dysfunction, which is a precursor to MODS. The measurable metrics from cardiac waveform analysis, such as HRV, BRS, and heart rate turbulence (HRT), can be integrated into predictive models. These models can then be used to develop CDS tools that help clinicians assess the risk of MODS development in real-time. Furthermore, the metrics from waveform analysis can be employed to create early warning scores that gage the risk of MODS, using established thresholds for parameters like HRV and BRS linked to adverse outcomes in sTBI patients. Therefore, this protocol for characterization of eAD using ECG and ABP waveforms offers a pathway toward the development of real-time CDS tools, predictive models, and clinical guidelines.

## Methods

2

### Recruitment

2.1

We will collect data from an ongoing multi-center randomized controlled trial examining the efficacy of a sTBI treatment strategy guided by both ICP and brain tissue oxygen (PbtO2) as compared to a strategy guided by ICP monitoring alone [Brain Oxygen Optimization in sTBI (BOOST), Phase 3, NCT03754114] (17). As part of the trial, the ECG waveform with four-leads and arterial blood pressure waveform data will be collected over the first 5 days of their intensive care unit (ICU) stay. Our ancillary study (AUTO-BOOST) will leverage this rich and granular waveform data to fully characterize autonomic dysfunction following sTBI.

We are sourcing data from this active clinical trial (BOOST), the trial has enrolled 550 patients. Since unexpected issues may arise during data collection, such as failures to collect data due to leads detaching or errors caused by device malfunctions, we estimate that approximately 50% of patients will have adequate cardiac telemetry data of sufficient quality for analysis. The Moberg monitor (CNS Monitor, Moberg ICU Solutions, Amber, Pennsylvania, United States) will capture and time-synchronize these analog data with other vital signs, ventilator data, and ICP/PbtO2 data, storing all data locally. A research team member will extract and upload the waveform data to a secure IBM cloud-based server. We will extract ABP, ECG data, and ventilator parameters from the Moberg device, deriving heart rate from the raw ECG tracing. We will use cleaned segments of stable recordings within 24 h of ICU admission for analysis.

### Data analysis

2.2

Based on data from the currently recruited 550 patients, we found some incomplete ECG recordings of short duration, necessitating data analysis based solely on the ABP signal. To address this issue, we will conduct the eAD characterization on two fronts: one from both ECG and ABP waveforms, and the other from only ABP waveforms.

We will conduct non-invasive characterization of eAD by computing multiple indices over 24 h following admission, including heart rate turbulence (HRT) (18), time- and frequency-domain analyses of HRV and sequence analysis of BRS. First, we will slice the long-monitoring waveform into 1-h segments and assess the signal quality for both ECG and ABP segments. Next, the premature ventricular contractions (PVC) detection will analyze high-quality ECG segments. If more than 10 PVC beats for a given 1-h segment are detected, we will conduct HRT analysis on ECG waveforms (19). HRT is generally assessed by two parameters: turbulence onset (TO) and turbulence slope (TS). TO measures the initial acceleration and subsequent deceleration of heart rate after a PVC, while TS quantifies the rate of heart rate return to baseline. We will extract two time series from the ECG and ABP waveforms: one consisting of RR intervals from normal sinus beats, and the other comprising systolic blood pressures (sBP) from ABP pulses. We will then perform three analyses on these sequences: extracting root mean square of successive differences (RMSSD) and HRT from time-domain RR interval sequences, transforming RR intervals into the frequency domain to calculate the low- and high-frequency band ratio, and estimating BRS indices from RR intervals and sBP sequences. For eAD characterization based on ABP signals alone, we will compute autonomic indices from pulse interval sequences, excluding HRT due to the difficulty of detecting PVC beats without ECG waveforms. Figure 1 summarizes the entire procedure, with detailed explanations of each function block provided in the following sections.

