#### Heart rate turbulence quantification

2.2.4

HRT refers to the fluctuations of sinus heart beat cycle length caused by PVC beats (18). When a PVC beat occurs, it results in a shortened interval with the prior beats and this interval is termed coupling interval (couplI). A longer interval than that of a normal sinus beat is then followed, which is a compensatory interval (compI) (36). The HRT reflects the natural fluctuation of HR after the compI. If more than 10 beats are detected as PVC, we will conduct HRT analysis to compute turbulence onset (TO) and slope (TS) (19) for each PVC beat. TO is an indicator to reflect the vagal inhibition by quantifying the initial fast increase of heart rate (36) and calculated as Equation 6:

(6)
$$TO=\frac{\left(RR_{1}+RR_{2}\right)-\left(RR_{-2}+RR_{-1}\right)}{RR_{-2}+RR_{-1}}\times 100\%$$

where 
$RR_{1},RR_{2}$
 are two RR intervals immediately after compI, and 
$RR_{-1},RR_{-2}$
 are two RR intervals immediately preceding couplI.

TS is an indicator to reflect the vagal activation and is measured as the maximum positive regression slope over any 5 consecutive sinus rhythm RR intervals within the first 15 RR intervals after the compI (19). Therefore, the analysis for both HRT parameters will require at least 2 sinus rhythm RR intervals before couplI and at least 15 RR intervals after compI. For 1-h ECG segments, we will compute the mean of TO and TS across all detected PVCs to obtain an average value that represents the overall heart rate turbulence for the recording period.

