## Discussion

5

This study’s novelty lies not in the development of new autonomic measures, but rather in three key aspects: (1) the first application of HRT analysis in sTBI patients, providing new insights into post-ectopic beat autonomic regulation in this population; (2) the comprehensive integration of multiple autonomic measures in a large cohort of sTBI patients, allowing for robust characterization of autonomic dysfunction patterns specific to this population; and (3) the potential to establish normative values and clinical thresholds for autonomic measures in acute sTBI, which are currently lacking. This approach will provide clinicians with a more complete understanding of autonomic dysfunction in sTBI and its relationship to clinical outcomes.

Following sTBI, eAD is a complex and multifaceted issue that can significantly impact a patient’s overall health and recovery. Characterizing eAD is crucial for risk assessment, customizing pharmacological interventions, and assessing rehabilitation strategies. While small studies indicate that eAD is associated with poor outcomes following sTBI, the duration and full trajectory of eAD has been poorly characterized. This protocol outlines the data analysis procedure for quantifying acute autonomic dysfunction using cardiac telemetry waveforms. We will collect and annotate waveform data from 550 patients in a clinical trial and quantify the incidence and magnitude of eAD indices after the first day of admission. We will characterize eAD as the presence of 3 or more indices less/greater than 2.5 SDs of age/sex-standardized values measured over 24 h following admission.

In some patients, simultaneous ECG and ABP signals may be unavailable. To solve this problem, we will divide the collected data into subgroups with and without ECG information and examine eAD within both subgroups. We will report results of the planned study in one or multiple scientific papers in international peer-reviewed journals. We will note and deviations from this protocol, if any occur, in these publications.

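### The more-than-10-PVC condition for HRT is applied to each single hour, although HRT enters the eAD rule as a 24-h index; scattered but usable PVCs then yield no HRT value

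*Protocol article*

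**What the plan says.** All places are in the protocol article.

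- **2.2 Data analysis** sets the 24-h window, "computing multiple indices over 24 h following admission, including heart rate turbulence (HRT" among them, and then the hourly unit: "First, we will slice the long-monitoring waveform into 1-h segments and assess the signal quality for both ECG and ABP segments". The condition for HRT follows: if more than 10 "PVC beats for a given 1-h segment are detected, we will conduct HRT analysis on ECG waveforms".
- **2.2.4 Heart rate turbulence quantification** restates the condition with no time unit: "If more than 10 beats are detected as PVC, we will conduct HRT analysis to compute turbulence onset (TO) and slope (TS"). It computes TO and TS for each PVC from 2 sinus intervals before the coupling interval and 15 intervals after the compensatory interval. It then summarises by the hour: "For 1-h ECG segments, we will compute the mean of TO and TS across all detected PVCs".
- **3 Statistical analysis** and **4 Expected results** use the first 24 h after ICU admission for the primary analysis. They define eAD as three or more of five indices beyond 2.5 SD; reduced HRT is one of the five.
- **5 Discussion** lists as the study's first novelty "the first application of HRT analysis in sTBI patients".

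**The concern.** The minimum count and the averaging work by the hour, but the index they feed is a 24-h index. A minimum count serves to steady an average. If the average that matters is the patient's 24-h value, the count belongs to the 24 h. Placed on the hour, it discards PVCs that have valid windows and could contribute.

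Two things follow. Some patients with enough PVCs over the day have no HRT value, so whether the index exists depends on how their PVCs are spread over clock hours. In the other patients HRT describes only the hours with more than 10 PVCs, whereas RMSSD, LF/HF and baroreflex sensitivity (BRS) carry no such condition. The indices combined in the three-of-five rule may then describe different hours of the same patient. At stake is the completeness and meaning of the measure that the Discussion puts first among the study's new contributions.

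**Working it through.** The article states no PVC rate and no expected HRT yield, so there is no figure of its own to reproduce.

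**Inputs from the article.** At least 11 PVCs in a 1-h segment (2.2); at most 24 segments in 24 h; only segments that pass the quality checks are kept (2.2.1), so usable hours may be fewer; 2 intervals before and 15 after each PVC (2.2.4).

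**Step 1: does the calculation need PVCs from the same hour?** Equation 6 for TO uses two intervals on each side of one PVC. TS uses the 15 intervals after one PVC. Both are then averaged over PVCs. Nothing in this refers to a clock hour.

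**Step 2: limiting case by counting.** The largest count with no qualifying hour is 10 × usable hours: 10 × 24 = 240. With 18, 12 or 6 usable hours it is 180, 120 or 60. The smallest count that gives a value is 11, all in one hour. With the same count pooled over 24 h, the largest number without a value is 10.

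**Step 3: size under assumed PVC processes.** Let X be the hourly count with mean m = (24-h mean)/24, hours independent, 24 usable hours. X is either Poisson (steady) or negative binomial with size 2, 1 or 0.3 (increasingly clustered). These are assumptions.

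- Probability that an hour qualifies: p = P(X ≥ 11).
- Probability that a patient has any HRT value: 1 − (1 − p)^24.
- Share of PVCs lying in qualifying hours: E[X; X ≥ 11] / m.

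Worked example, Poisson with 120 per 24 h: m = 5, p = 0.0137, so 1 − (1 − 0.0137)^24 = 0.28; share of PVCs used 3.2%.

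Patients with any HRT value under the hourly condition:

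| Mean PVCs per 24 h | Poisson | NB size 2 | NB size 1 | NB size 0.3 |
|---|---|---|---|---|
| 48 | 0.02% | 7% | 24% | 65% |
| 120 | 28% | 92.5% | 97% | 98% |
| 240 | about 100% | about 100% | about 100% | 99.9% |

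Share of PVCs in qualifying hours at 120 per 24 h: 3%, 29%, 43% and 69% in the same order.

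Further Poisson points: 72 per 24 h gives 0.7% of patients a value, 96 gives 6.6%, 144 gives 65% (8.4% of PVCs used) and 192 gives 99%.

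**Step 4: the same count pooled over 24 h.** At a mean of 48 per 24 h or more, at least 99.7% of patients exceed 10 PVCs under all four models, before the requirement of a valid window around each PVC.

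**The case against.** The strongest reply is that the hour is the stated unit of the whole pipeline, not a slip confined to HRT: the Figure 1 legend and the coherence analysis (2.3) also work on 1-h segments. Hourly values suit the aim of real-time decision support (1.3). The Introduction describes autonomic state as changing with intracranial pressure, sedation and vasopressors, and pooling over 24 h averages across those changes. A minimum count per hour also prevents an hourly mean that rests on one or two PVCs. The count is taken from a cited source that is not at hand, so whether that source counts per hour or per recording cannot be judged.

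This justifies keeping an hourly HRT with its hourly condition. It does not justify using that condition to decide whether the 24-h index exists. The averaging over changing states is a real cost of pooling and is counted as such under the fix.

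It might also be said that 2.2.4, read alone, allows a pooled count. Section 2.2 ties the count to a 1-h segment, and the hourly averaging in 2.2.4 agrees with it. At the least the two sections need reconciling.

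A reader might infer more than the article supports:

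- *That patients with around 240 PVCs commonly lose HRT.* That count needs exactly 10 in each of 24 usable hours. At a mean of 240, nearly every patient gets a value under all four models.
- *That most usable PVCs are discarded.* At 120 per 24 h the share used runs from 3% to 69%, depending on clustering.
- *That HRT is measured only in bursts, at the height of catecholamine drive.* Eleven PVCs in an hour is about one every 5.5 minutes (60/11), a patient above 10 in every hour is measured throughout, and the article nowhere links hourly PVC counts to catecholamines.

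**Conclusion.** The point holds and should be changed before analysis. The rule as stated does not fit the index it serves, and this is more than detail left to a fuller plan, because following the stated rule removes HRT from patients whose recordings could supply it.

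The loss falls mainly on patients with more than 10 PVCs in the window but moderate counts, roughly 11 to 120 per 24 h depending on clustering. Steady ectopy costs the most patients. Clustered ectopy leaves more patients with a value but draws it from the hours with more than 10 PVCs only. How many patients in this cohort are affected cannot be said: the PVC rates, the clustering, the independence of hours and the 24 usable hours are all assumptions.

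**What to change.** For the primary 24-h HRT index, apply the more-than-10 count to all PVCs that have the required 2 preceding and 15 following intervals, pooled over the patient's quality-passed ECG hours in the first 24 h. Compute one mean TO and one mean TS per patient from that pool. Align 2.2 and 2.2.4 so that both give the same unit for the count and for the averaging. Keep hourly HRT, with its hourly condition, as descriptive output.

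The cost is a change of wording and a small code change, with no new data. No extra PVC location is needed, because 2.2.3 already locates PVCs on every segment classified as containing them; only the TO and TS step is conditional. The drawback is that the pooled value averages over changing clinical states within the 24 h, which the retained hourly output helps to show.
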